***Sample Size***

To determine the necessary sample size, with a confidence level of 95%, a test power of 80%, and assuming that the effect size (Cohen's d) of the intervention compared to the control group is 0.7 [22,23], the minimum sample size required for each group is calculated to be 32 participants. Considering a 10% dropout rate, the sample size for each group will be set at 35 participants.

n = (2 × (z _(1-α/2)_ + z _(1-β)_))^2^ / (E × S)^2^ = (2 × (1.96 + 0.84))^2^ / (0.7)^2^ = 32

z _(0.975)_ = 1.96

z _(0.8)_ = 0.84

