**Abstract**

**Background:** The human papillomavirus (HPV) is the most common sexually transmitted infection worldwide. The present study aims to examine the impact of an educational intervention based on the Health Belief Model (HBM) on sexual self-care among women of reproductive age infected with HPV.

**Method:** This is a randomized controlled trial with two parallel groups. Seventy women with HPV will be selected through simple random sampling from Arash Women's Comprehensive Hospital and Imam Khomeini Hospital in Tehran, Iran and will be allocated to a control group (n = 35) and an intervention group (n = 35). Participants in the intervention group will receive HBM-based sexual self-care education in four 45-60 min weekly sessions which will be held using the lectures, group discussions, question & answer sessions, PowerPoint presentations, pamphlets, educational videos, and role-playing. Data will be collected through a Demographic and obstetric information questionnaire, The Sexual Self-Care and HBM questionnaires, and will be analyzed through the ANOVA, Friedman test, and logistic regression modeling. All statistical analyses will be performed using SPSS version 24.

**Discussion:** Upon completion of this study, an increase in sexual self-care scores may indicate the effectiveness of this educational intervention. If proven effective, it can be recommended as a cost-effective method to achieve this goal, and it can be utilized by health professionals, including midwives and counselors to enhance sexual self-care among these women.

**Key-words:** Sexual Self-Care, Human Papillomavirus, Women, Health Belief Model, Intervention, Clinical trial

**Ethical code:** IR.TUMS.FNM.REC.1402.186

**Trial registration:** This study was registered in the Iranian Registry of Clinical Trials on 2024/01/01 (code: IRCT20231223060503N1)

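### The sample-size equation is misprinted: it evaluates to 64, although 32 per group is right for the stated inputs, and 35 per group falls just short of 32 after 10% dropout

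*Protocol*

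**What the plan says.** The Sample Size section of the protocol assumes that "the effect size (Cohen's d) of the intervention compared to the control group is 0.7", with 95% confidence and 80% power, and concludes that "the minimum sample size required for each group is calculated to be 32 participants". It then prints the formula twice on one line, first in symbols and then with numbers. The numerical form ends "2 × (1.96 + 0.84))^2^ / (0.7)^2^ = 32". In both forms a bracket opens before the 2 and closes just before the exponent, so the exponent covers the 2 as well as the sum of the two normal quantiles. The symbolic denominator is the square of E × S. Neither letter is defined, and only 0.7 is substituted.

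For losses, the section says: "Considering a 10% dropout rate, the sample size for each group will be set at 35 participants". The Abstract and the participant flow figure carry the same size, 35 per group and 70 randomised.

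**The concern.** This line is the only quantitative justification for randomising 70 women. Anyone who evaluates it as printed gets twice the stated answer, and the section does not say whether the equation or the result is at fault.

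The step from 32 to 35 raises a second, independent question. The protocol calls 32 a minimum, so the inflated number should still leave at least 32 women per group after the assumed loss. The Data management and analysis section specifies a per-protocol analysis, and the Exclusion Criteria remove women for missed sessions, faulty questionnaires or withdrawal. Losses therefore come straight off the analysed number. What is at stake is whether the stated 80% power is met on the plan's own assumptions, and by how much it is missed if not.

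**Working it through.** **Inputs**, all from the Sample Size section: z(0.975) = 1.96 (two-sided 5%), z(0.80) = 0.84, d = 0.7, equal groups, 10% dropout, 35 per group enrolled.

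**1. The plan's own figure.** The standard normal-approximation formula for two means is n per group = 2 × (z(1−α/2) + z(1−β))² / d².

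2 × (1.96 + 0.84)² / 0.7² = 2 × 7.84 / 0.49 = 15.68 / 0.49 = **32.0**

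The stated 32 is reproduced exactly. With unrounded quantiles the result is 32.04, which would strictly round up to 33; that difference is only rounding.

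**2. The equation as printed.**

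(2 × 2.80)² / 0.49 = 5.60² / 0.49 = 31.36 / 0.49 = **64.0**

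Squaring the 2 turns a factor of 2 into a factor of 4, which doubles the answer.

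**3. Is 64 the required size?** No. At d = 0.7, 64 per group would give 97.7% power by the normal approximation and 97.6% by the t test, far above the 80% target.

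**4. The dropout step.** The number to enrol so that 32 remain after 10% loss is 32 / 0.9 = 35.56, so 36. The cruder route, 32 × 1.1 = 35.2, also gives 36 when rounded up. The other way round, 35 × 0.9 = 31.5, half a participant per group below 32.

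**5. Power with the numbers that remain.** The normal approximation is Φ(d × √(n/2) − 1.96). For n = 31.5 this is Φ(0.7 × 3.969 − 1.96) = Φ(0.818) = 79.3%. The t-test column uses the noncentral t distribution, two-sided 5%, unadjusted.

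| Evaluable per group | Normal approximation | Two-sample t test |
|---|---|---|
| 31 | 78.7% | 77.4% |
| 31.5 | 79.3% | 78.1% |
| 32 | 80.0% | 78.7% |
| 35 (no loss) | 83.4% | 82.3% |

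The t-based solution for 80% power is n = 33.02, so 34 per group.

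**The case against.** The strongest reply is that nothing of substance went wrong. The inputs, the result and the enrolment figures agree with one another, and the misplaced bracket did not carry through to any number that the trial uses. The normal approximation is an accepted planning method, and on it 32 per group gives 80.0% power. Moving from 32 × 1.1 = 35.2 to 35 is ordinary rounding. The gap of one woman per group is small beside the uncertainty in an assumed d and an assumed dropout rate. Most of this stands, and it is why the point is minor. It does not rescue the equation, which is false as printed in both its forms, and a quantity described as a minimum should be rounded up.

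Three stronger readings are tempting, and the document does not support them:

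- **The trial needs 64 per group, or is half the size it should be.** A reader who trusts the printed line might infer this. The protocol's own inputs in the standard formula give 32.0, so the fault lies in the notation.
- **The plan is materially underpowered because its test needs 34 per group.** That figure assumes a single unadjusted two-group comparison. The Data management and analysis section names ANOVA but does not tie the primary comparison to one of the three assessment times. The t-based figures are a useful cross-check and do not show that the protocol's method is wrong.
- **The denominator contradicts the use of a standardised effect.** E and S are undefined. If E is the standardised effect and S is 1, their product is the 0.7 that was substituted. The fault is an unlabelled symbol.

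**Conclusion.** Minor, but wrong as written. The printed expression equals 64 where the protocol states 32, because the factor 2 is inside the square. The requirement of 32 per group is correct by the normal approximation for d = 0.7, two-sided 5% and 80% power.

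The dropout allowance is rounded down. It is one participant per group short of 36 and leaves an expected 31.5 against a stated minimum of 32. At 31.5 per group the shortfall from 80% power is 0.7 of a percentage point on the protocol's own method (79.3%) and 1.9 points by an unadjusted t test (78.1%). It reaches 2.6 points only with 31 per group and the t test (77.4%).

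These figures take the protocol's d of 0.7 and 10% loss as given and assume equal losses in the two groups. They say nothing about whether either assumption is realistic.

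**What to change.** Make these text changes in the Sample Size section:

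- Print the formula with the 2 outside the square: n = 2 × (z(1−α/2) + z(1−β))² / d² = 2 × (1.96 + 0.84)² / 0.7² = 32 per group, and say that this is the normal approximation. If E and S are kept, define them.
- Replace the implied claim of 80% power after dropout with what 35 per group delivers. With 10% loss, 31–32 women per group are evaluable. Power at d = 0.7 is then about 79% by the normal approximation (79.3% at 31.5), or about 77–79% by an unadjusted two-sample t test (77.4% at 31, 78.1% at 31.5, 78.7% at 32).

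The cost is about two lines of protocol text and a slightly less favourable power figure. Enrolment, design and conduct do not change.

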***Randomization and allocation***

Participants will be randomly assigned to either the intervention or control group using a block randomization method with a block size of four. The letter A represents the intervention group, and the letter B represents the control group. All possible permutations of the letters AA and BB will be listed, resulting in six different combinations (AABB, BBAA, ABAB, BAAB, ABBA, BBBA). One combination will be randomly selected from these six permutations. For example, if the combination AABB is chosen, it means that the first and second participants will be assigned to the intervention group, and the next two participants will be assigned to the control group. This process will continue until the sample size is reached.

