***Sampling method***

After the study proposal is approved by the Ethics Committee of Tehran University of Medical Sciences, and after obtaining a Clinical Trial Registration Code (IRCT) and a written letter of introduction, eligible women will be enrolled in the study. Ethical conditions and considerations will be explained, and written informed consent will be obtained from those willing to participate. The researcher will first provide detailed information about the study, including its title, objectives, inclusion criteria, and the study's procedures. Participants will then be randomly assigned to either the intervention or control group using block randomization. Specifically, volunteers who agree to participate will be randomly allocated to the intervention or control groups using a block size of four. The educational intervention will be conducted in person. The intervention group will receive training based on the Health Belief Model, focusing on its constructs, in four sessions of 45-60 minutes each, held once a week with groups of 10-15 participants. This training will be provided by the researcher. The control group will receive routine care. The questionnaires will be administered to participants in both groups at three time points: before the intervention, immediately after, and 8 weeks post-intervention. To adhere to ethical considerations, the control group, if interested in receiving the training, will be provided with educational pamphlets and CDs after the intervention is completed. Figure 2 shows the schedule of enrolment, intervention, and assessment.

Figure 2. Schedule of enrolment, interventions, and assessments

|  | **STUDY PERIOD** | | | | | | | |  |
| --- | --- | --- | --- | --- | --- | --- | --- | --- | --- |
|  | **Enrolment** | **Allocation** | **Post-allocation** | | | | **Close-out** | |  |
| **TIMEPOINT**** | ***-t_1_*** | **0** | ***t_1_*** | ***t_2_*** | ***t_3_*** | ***t_4_*** | | ***t_5_*** | |
| **ENROLMENT:** |  |  |  |  |  |  | |  | |
| **Eligibility screen** | X |  |  |  |  |  | |  | |
| **Informed consent** | X |  |  |  |  |  | |  | |
| ***Randomized by independent person*** | X |  |  |  |  |  | |  | |
| **Allocation** |  | X |  |  |  |  | |  | |
| **INTERVENTIONS:** |  |  |  |  |  |  | |  | |
| ***Group A: educational intervention*** |  |  |  |  |  |  | |  | |
| ***Group B: control*** |  |  |  |  |  |  | |  | |
| **ASSESSMENTS:** |  |  |  |  |  |  | |  | |

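### The printed list of randomisation blocks has BBBA where BABA belongs; used as printed, it allocates 45.8% rather than 50% of women to the intervention

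*Protocol*

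**What the plan says.** The Randomization and allocation section of the Protocol allocates women "using a block randomization method with a block size of four", and the Sampling method section repeats that block size. The coding is explicit: "The letter A represents the intervention group, and the letter B represents the control group". The rule for building blocks is "All possible permutations of the letters AA and BB will be listed", and the list that follows is given as "resulting in six different combinations (AABB, BBAA, ABAB, BAAB, ABBA, BBBA". From this list, "One combination will be randomly selected from these six permutations", and "This process will continue until the sample size is reached". The Abstract and Figure 1 plan 35 women per arm.

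Under Allocation concealment and blinding, a colleague outside the study creates the sequence and puts it in opaque, numbered envelopes opened in order. The same section says that researchers and participants cannot be blinded. Under Sampling method, the researcher explains the study to candidates, and of the intervention the section says "This training will be provided by the researcher".

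**The concern.** The rule and the list disagree. Any ordering of two As and two Bs has two of each, but BBBA has one A and three Bs. A colleague who works from the printed list would be sampling from a set that favours control, and neither the stated equal allocation nor the balance that blocking is meant to give would hold.

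A second, smaller issue sits in the same section. All blocks have one size, and that size is disclosed. Someone who knows the earlier assignments in a block can sometimes work out the next one, even though the envelopes are opaque. In a trial where the researcher is not blinded, that leaves some room for selective enrolment.

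**Working it through.** **Inputs.** Block size 4, coding and printed list: Randomization and allocation. Total 70, planned 35:35: Abstract and Figure 1. Effect size d = 0.7, 95% confidence, 80% power, 10% dropout: Sample Size. Assumption: each block is a fresh draw with probability 1/6 per listed block.

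**The plan's own figure.** The standard formula gives n = 2 × (1.96 + 0.84)² / 0.7² = 2 × 7.84 / 0.49 = 32 per group, as stated. Adding 10% gives 32 × 1.1 = 35.2, against the stated 35.

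**The list.** The orderings of two As and two Bs number 4!/(2! × 2!) = 6: AABB, ABAB, ABBA, BAAB, BABA, BBAA. The printed list lacks BABA and has BBBA in its place.

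**Chance of intervention as printed.** Five blocks hold 2 As and one holds 1, so the list has 11 As in 24 places: 11/24 = 45.8%.

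**Expected split at 70.** Seventy women fill 17 blocks and two places of the 18th (17 × 4 + 2 = 70).
- 17 full blocks: 17 × 11/6 = 187/6 As.
- First two places of block 18: A has probability 1/2, then 1/3, so 5/6 As.
- Total: 192/6 = 32 intervention, 38 control.

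**Chance of exactly 35:35.** Let K be the number of BBBA blocks among the 17. The intervention arm is 34 − K plus the As in the first two places of block 18. Those places hold 0, 1 or 2 As with probability 2/6, 3/6 and 1/6.
- K = 0: (5/6)^17 = 0.0451, times 3/6 = 0.0225.
- K = 1: 17 × (1/6) × (5/6)^16 = 0.1532, times 1/6 = 0.0255.
- Sum: 0.0481, or 4.8%.

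At least one BBBA block occurs with probability 1 − 0.0451 = 95.5%. The full exact distribution gives fewer than 35 in the intervention arm in 94.4% of trials, and 32 or fewer in 59.7%.

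**Power at d = 0.7 (two-sided t-test, before dropout).**

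| Split | Power |
| --- | --- |
| 35:35 | 82.3% |
| 32:38 | 82.0% |
| 28:42 | 80.7% |

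The reason is that the total stays at 70. The equivalent equal-arm size at 32:38 is 2 × 32 × 38 / 70 = 34.7, against 35.

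**With BABA restored.** Seventeen balanced blocks give 34:34. The next two places are AA (1/6), BB (1/6) or mixed (4/6). So 35:35 has probability 66.7%, and 36:34 and 34:36 have 16.7% each. No larger imbalance is possible.

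**Predictability with the correct list.** After AA or BB, places 3 and 4 are certain; in the other four blocks only place 4 is. Certain places: (2 + 2 + 1 + 1 + 1 + 1)/24 = 8/24 = one third. The best guess is right with probability 1/2, 2/3, 2/3 and 1 at the four places, on average 70.8%. The printed list gives the same two figures, so correcting BBBA does not change predictability.

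**The case against.** The strongest reply is that BBBA is a typing error and the design is sound. The stated rule produces BABA and cannot produce BBBA, so a colleague who follows the sentence and not the list will build the right sequence. That is likely, and every imbalance figure above depends on the printed list reaching the envelopes. What remains is that the Protocol prints an operative randomisation list that is wrong, with no other text to override it.

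A reader might infer that the intervention arm, falling to 32 or fewer, leaves the trial underpowered. The documents' own figures do not support this. The control arm grows as the intervention arm shrinks, and the expected loss is 0.3 percentage points. Nor do arms that are unequal by chance bias the comparison in themselves.

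A reader might also infer that the unblinded recruiter can foresee allocations. The Protocol does not say so. Sampling method puts enrolment in the passive and names the researcher only for informing candidates and delivering the training. Figure 2 lists randomisation by an independent person, and no section says who opens the envelopes. Even for someone who knows the block size, where blocks begin and every earlier assignment in the block, one third of assignments are certain, not all. If one envelope series serves both hospitals, tracking is harder still. Independent generation and opaque numbered envelopes are real safeguards, but they do not stop deduction from past assignments.

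**Conclusion.** The list is wrong as written and should be corrected. Assuming it is used literally with a fresh equal draw per block, allocation is 45.8% to intervention, the expected split is 32:38, and 35:35 occurs in about 5% of trials. The damage is to the stated 1:1 allocation and to block balance; the effect on power is negligible.

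The text also leaves open whether one block is drawn per four women or drawn once and repeated. On the second reading, BBBA would give 17 As and 51 Bs in 17 blocks plus two more Bs, that is 17:53, and every assignment after the first block would be known. The sentence about the process continuing favours the first reading but does not settle it.

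Predictability is a secondary and partial weakness. The one-third figure is firm. That the unblinded researcher could be the one to use it is suggested by the documents, not stated.

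**What to change.** **Needed.** Replace BBBA with BABA. State that each block is a new random draw from the six. Check any envelopes already prepared against the corrected list, and report which list was used. Say that the arms may end at 34:36, because 70 is not a multiple of four. The cost is a one-letter correction and two sentences, plus a check of the envelopes if they exist.

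**Recommended.** State who enrols women and who opens the envelopes. Have the independent colleague use randomly varying balanced blocks (for example 4 and 6) in a single series, with the sizes withheld from whoever enrols. The downside is small: an unfinished block of six can leave the arms up to 3 women apart. At exactly 70, an unfinished block has 2 or 4 places filled, because all block sizes are even. The worst starts are then AA or AAAB (or their mirror images), each 2 apart, so the arms stay within 34:36.

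A separate series per hospital is not needed to cure this defect. If one is used with blocks of up to six, each series can stop 3 apart in the same direction, so the stated range would have to widen to 32:38.

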***Allocation concealment and blinding***

To ensure allocation concealment, a colleague not involved in the study will create the allocation sequence and write it on pieces of paper. These papers will be placed in opaque envelopes, which will then be sequentially numbered. The envelopes will be opened in order to assign participants to their respective groups. Although blinding of researchers and participants is not feasible due to the nature of the intervention, the outcome evaluator will remain blinded by having a separate colleague handle data collection.

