***Study setting***

The setting of the study will be Arash Women's Comprehensive Hospital and Imam Khomeini Hospital. These clinics have been selected as referral hospitals in central and eastern Tehran, Iran.

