***Participants***

Participants will be women with HPV who visit the women’s clinics at Arash and Imam Khomeini hospitals and meet the study inclusion criteria.

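### Women are recruited at two hospitals, but allocation is a single blocked sequence not stratified by hospital, and how the clinics share the envelopes is not stated

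*Protocol*

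**What the plan says.** - Protocol, *Study setting*: "The setting of the study will be Arash Women's Comprehensive Hospital and Imam Khomeini Hospital". *Participants* describes the sample as "women with HPV who visit the women’s clinics at Arash and Imam Khomeini hospitals and meet the study inclusion criteria". Neither section gives a target or an expected number per hospital.
- *Sampling method*: "The control group will receive routine care". What this care consists of is not described, either overall or by hospital.
- *Randomization and allocation*: women are "randomly assigned to either the intervention or control group using a block randomization method with a block size of four". A block is drawn from six listed, applied to participants in order, and "This process will continue until the sample size is reached". The six printed blocks are AABB, BBAA, ABAB, BAAB, ABBA and BBBA.
- *Allocation concealment and blinding*: "a colleague not involved in the study will create the allocation sequence and write it on pieces of paper", with the sequence in the singular. Then: "These papers will be placed in opaque envelopes, which will then be sequentially numbered. The envelopes will be opened in order". The sentence goes on to give the purpose of assigning women to groups.

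No section names hospital as a stratum, provides a list or envelope set per hospital, or says who holds the envelopes, where they are kept, or how the next number is issued when women enrol at two clinics. Figure 2 attributes randomisation to an independent person but does not say whether that person serves both sites.

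**The concern.** Blocking on overall order of entry balances the arms in total, not within a hospital. With 35 women per arm, chance alone can give the arms noticeably different hospital mixes. If sexual self-care scores (FSHS) differ between hospitals, that mix moves the observed arm difference, and the between-hospital variation adds to the error of an unadjusted comparison.

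There is also an operational gap. Numbered opaque envelopes are the stated safeguard for concealment, the researchers are not blinded, and the block size is fixed. If a single series is shared or divided informally between two clinics, the link between envelope number and order of entry can be lost. Sequence generation and envelope handling are protocol matters, set out here in some detail, and they cannot be repaired once allocation has begun.

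**Working it through.** **Inputs.** From the Protocol: two hospitals; 35 per arm, 70 in total; blocks of four; d = 0.7; "with a confidence level of 95%, a test power of 80"%. Assumed, because the Protocol gives neither: a hospital split between 35:35 and 25:45, and a difference in mean FSHS between hospitals of 0.3 to 0.5 within-hospital SD.

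**1. The plan's own figure.** 2 × (1.96 + 0.84)² / 0.7² = 15.68 / 0.49 = 32 per group, as stated. (The formula as printed puts the 2 inside the square, which would give 64; that is a separate matter.) Allowing for dropout, 32 / 0.9 = 35.6 and 32 × 1.1 = 35.2, against 35 stated. Stratifying does not change the required size.

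**2. Chance difference in hospital mix, no stratification.** Let k be the number of women from hospital 1 in one arm, out of s from that hospital. With 35 of 70 in each arm, k is hypergeometric and the arm difference in hospital share is (2k − s)/35.

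- Split 35:35: SD of k = √(35 × 0.5 × 0.5 × 35/69) = 2.11. SD of the difference = 2 × 2.11/35 = 0.120, or 12 percentage points.

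| Hospital split | P(difference ≥ 10 points) | P(difference ≥ 20 points) |
|---|---|---|
| 35:35 | 0.34 | 0.15 |
| 34:36 | 0.47 | 0.09 |
| 28:42 | 0.46 | 0.09 |
| 26:44 | 0.46 | 0.08 |
| 25:45 | 0.32 | 0.13 |

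The results alternate because the difference moves in steps of 2/35. With an odd s, the first value above 10 points is 5/35 = 14.3; with an even s it is 4/35 = 11.4. Over all splits from 35:35 to 25:45 the ranges are 32 to 47% and 8 to 15%.

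Simulating the described method directly (balanced blocks of four cut at 70, so the arms may end 34:36; 40,000 sequences for each of seven splits) gives 37 to 43% and 9 to 13%.

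**3. One blocked list per hospital.** With balanced blocks, only the last, incomplete block at a hospital can be uneven, by at most 2 women. In simulation the SD of the difference in hospital share falls to about 2 points or less, and it never exceeded about 3 points.

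This fails with the blocks as printed, because BBBA holds one A and three B. Each BBBA adds 2 to the imbalance, so two or more of them exceed 2 women. At a hospital with m complete blocks that probability is 1 − (5/6)^m − m(1/6)(5/6)^(m−1):

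- 28 women (m = 7): 0.33
- 40 women (m = 10): 0.52

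In simulation it reaches about 0.7 at 45 women. Across the trial, the expected number in the intervention arm would be 70/4 × 11/6 = 32, against 38 in control.

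**4. What it costs the comparison.** The standard error of the arm difference is √(2/35) = 0.24 SD.

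- Typical (1 SD) imbalance with a 0.5 SD hospital difference: 0.12 × 0.5 = 0.06 SD.
- A 20-point imbalance: 0.20 × 0.3 = 0.06 SD to 0.20 × 0.5 = 0.10 SD, or 9 to 14% of the planned 0.7.

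Type I error of the unadjusted test, simulated at both splits and both hospital effects: 0.050 to 0.052.

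Power at 0.7 within-hospital SD with all 70 analysed (noncentral t, 35:35 split; unadjusted variance 1 + g²/4, where g is the hospital difference):

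| g | Unadjusted | Stratified, hospital in model | Cost |
|---|---|---|---|
| 0.3 | 0.815 (variance 1.0225) | 0.823 | 0.8 points |
| 0.5 | 0.800 (variance 1.0625) | 0.823 | 2.3 points |

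Simulated trials agree: 0.80 to 0.81 against 0.82.

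**The case against.** Unstratified blocked randomisation in a two-centre trial is valid. The chance imbalance in hospital mix is already part of the standard error, and a shift of 0.06 SD is small against 0.24 SD. That stands, and it limits the point to precision and credibility.

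A reader might infer that one numbered series cannot be followed at two sites. The Protocol does not support this. A single holder, or a central point contacted at each enrolment, could run it in sequence, and the text is compatible with one researcher informing and enrolling women at both hospitals. The envelope sentence may also be stating a purpose rather than an order of opening; the order then rests on the sequential numbering and on the worked example of a block. What remains is that the handling across two clinics is not described.

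A reader might also infer that routine care differs between the hospitals and so differs between the arms. No section says so. Both are described as referral hospitals, their clinics come under one university, and no scores are given by hospital. The 0.3 to 0.5 SD range is an assumption.

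Finally, model terms may be set in a statistical analysis plan that is not at hand. The silence of *Data management and analysis* about hospital is therefore not a fault in itself.

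**Conclusion.** The point holds as a modest design improvement. The Protocol recruits at two hospitals, describes one unstratified blocked sequence, and leaves the sharing of the envelopes unstated. If the hospital split lies between 35:35 and 25:45, the arms will differ in hospital share by 10 points or more in about a third to just under half of randomisations, and by 20 points or more in about 8 to 15%.

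It should not be read as bias or as an inflated false-positive rate: the imbalance is random, and type I error stays near 0.05. Under an assumed hospital difference of 0.3 to 0.5 SD the cost is about 1 to 2 points of power, plus a comparison that is harder to defend if the mix happens to be uneven. If the hospitals have the same mean score, there is no cost in power. Nor does a list per hospital by itself guarantee balance to within 2 women; that needs balanced blocks.

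**What to change.** 1. In *Randomization and allocation*, correct the printed block BBBA to BABA, so that all six blocks hold two of each letter.
2. In the same section and in *Allocation concealment and blinding*, have the independent colleague prepare one blocked sequence and one separately numbered set of opaque envelopes per hospital, each opened in number order at that hospital. Central allocation stratified by hospital would serve equally well. State who holds and opens the envelopes.
3. Include hospital as a fixed factor in the between-arm analysis, in *Data management and analysis* or in the statistical analysis plan.

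Cost: a second list and envelope set, 1 degree of freedom, and possibly one incomplete block per hospital. No extra participants are needed. One drawback is that, with a fixed block size of four, allocations within a hospital become slightly easier to predict than in a series that mixes both hospitals.
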